## Abstract

**Background:**

A cancer diagnosis is 2.9 times more likely to occur during the adolescent and young adult years than in younger children. This spike in incidence coincides with a life stage characterised by psychological vulnerability as young people strive to attain numerous, critical developmental milestones. The distress young people experience after cancer treatment seriously jeopardises their ability to move into well-functioning adulthood.

**Methods/Design:**

This article presents the protocol of the Recapture Life study, a phase II three-arm randomised controlled trial designed to evaluate the feasibility and efficacy of a new intervention in reducing distress and improving quality of life for adolescent and young adult cancer survivors. The novel intervention, “ReCaPTure LiFe” will be compared to a both a wait-list, and a peer-support group control. Ninety young people aged 15–25 years who have completed cancer treatment in the past 1–6 months will be recruited from hospitals around Australia. Those randomised to receive Recapture Life will participate in six, weekly, 90-minute online group sessions led by a psychologist, involving peer-discussion around cognitive-behavioural coping skills (including: behavioural activation, thought challenging, communication and assertiveness skills training, problem-solving and goal-setting). Participants randomised to the peer-support group control will receive non-directive peer support delivered in an identical manner. Participants will complete psychosocial measures at baseline, post-intervention, and 12-months post-intervention. The primary outcome will be quality of life. Secondary outcomes will include depression, anxiety, stress, family functioning, coping, and cancer-related identity.

**Discussion:**

This article reviews the empirical rationale for using group-based, online cognitive-behavioural therapy in young people after cancer treatment. The potential challenges of delivering skills-based programs in an online modality are highlighted, and the role of both peer and caregiver support in enhancing the effectiveness of this skills-based intervention is also discussed. The innovative videoconferencing delivery method Recapture Life uses has the potential to address the geographic and psychological isolation of adolescents and young adults as they move toward cancer survivorship. It is expected that teaching AYAs coping skills as they resume their normal lives after cancer may have long-term implications for their quality of life.

**Trial Registration:**

ACTRN12610000717055

## Background

### The mental health burden of cancer in adolescents and young adults

Cancer is 2.9 times more likely to be diagnosed in people aged 15–29 years than during the first 15 years of life 
[1,2]. Improvements in medical treatments mean that there is now a growing population of survivors in the adolescent and young adult (AYA) age range 
[3]. As the peak period for the onset of mental health problems coincides with the AYA period 
[4], a cancer diagnosis during these years can have a far-reaching impact. Well beyond treatment completion, cancer may disrupt AYAs’ ability to attain the individual and interpersonal skills that are necessary to function well as they mature 
[5,6]. Failing to achieve these critical milestones places young people at a significant risk for poor adaptation within their future adult roles 
[7].

Although most AYAs will adapt well into long-term cancer survivorship 
[8], as a group they experience more complex, more severe, and longer-lasting distress than do children or adults with similar diagnoses 
[9-11]. This distress tends to be worse after cancer treatment completion than at any other stage of their cancer trajectory 
[12-16]. Among long-term survivors of adolescent cancer, the prevalence of clinical disorders such as anxiety, depression, or post-traumatic stress disorder (PTSD) has been shown to be as high as 24.3%, with subclinical distress also prevalent (22.4%) 
[16]. Adolescent cancer survivors also report having a worse quality of life (QoL) than both survivors of childhood cancer 
[17], or their age-matched healthy peers 
[18]. Without intervention, these mental health issues pose a significant threat to survivors’ longer term psychological adjustment.

Evidence-based, age-appropriate psychosocial support for surviving AYA cancer patients is therefore strongly indicated 
[13]. Despite this, recent reports indicate that young people living with cancer receive little post-treatment support from the hospital environment, and find supportive care resources in community settings difficult to locate and access 
[19]. Consequently, AYAs report experiencing high levels of unmet needs, and subsequently, higher levels of distress 
[6,20-22]. This is despite the existence of evidence-based psychological therapies that could be used to assist AYAs’ positive transition to survivorship.

### Efficacy of cognitive-behavioural therapy for adolescents and young adults

Cognitive-behavioural therapy (CBT) is a ‘talking therapy’ that involves training the client to recognise, and change, maladaptive thinking styles 
[23]. Extensive evidence supports the efficacy of CBT in treating both anxiety 
[24,25] and depression 
[25,26] in non-cancer affected adolescents. CBT is also efficacious in preventing the development of anxiety and depression among young people who show sub-clinical distress; one meta-analysis of 130 studies showed that such programs typically achieve at least moderate sized effects 
[27,28].

As yet, no studies have examined the efficacy of group-based CBT in a population of AYAs with cancer. Pilot data suggests, however, that AYAs with cancer respond positively to CBT skills and are enthusiastic to incorporate these skills into their daily life 
[19]. Consistent with this, one recent review of interventions for AYAs with chronic illnesses (including cancer) found that multi-session, skills-based interventions can be highly effective in treating emotional or behavioural problems in this age group, yielding medium to large effect sizes 
[29]. Together, these data recommend CBT as a promising, yet untested, form of psychological intervention in AYAs living with cancer.

### The importance of therapy modality: group-based peer support and ‘e-therapy’ in adolescents and young adults

Peer support groups (PSGs) for cancer patients and survivors remain the most prevalent form of psychological support available 
[30]. However, as a form of psychological support, their effects are largely unquantified; the few that have been formally evaluated tend to show small/mixed effects among AYAs 
[29,31]. Despite this, PSGs may address the sense of isolation and developmental disconnection with same-aged peers created by their small, dispersed numbers while on treatment 
[32]. Indeed, AYAs are highly receptive to PSGs as a form of intervention 
[19,33,34]. The extent to which peer discussion drives positive adaptation among AYAs is therefore important to assess.

AYAs’ geographic and demographic isolation demands innovative solutions to facilitate supportive, peer-based interactions. Healthy AYAs and those living with cancer are heavy users of the internet (reporting 1–3 hours daily use), and already seek and receive many of their peer interactions online 
[35,36]. Computer-based ‘e-therapies’ delivered online have been hailed as a new way to overcome issues of equity in accessibility and the stigma associated with seeking help from mental health professionals for young people 
[37-39]. Computer-based CBT has demonstrated moderate to very large effects in treating anxiety and mood disorders among adults 
[40] and also appears efficacious among children and adolescents 
[41]. It follows, then, that CBT delivered online to AYAs recovering from cancer may be effective.

## Methods/Design

The Recapture Life-AYA study is a multi-site, phase II randomised controlled trial (RCT) to assess the feasibility and efficacy of a new, online, CBT-based intervention for AYAs after cancer treatment. AYAs aged 15–25 years at treatment completion will be recruited and randomised to one of three treatment arms: Recapture Life-AYA, a peer-support group (PSG) control, and a six week waitlist control group. The novel intervention, named **‘ReCaPTure LiFe-AYA’** (**R**esilience and **C**oping skills for young **P**eople and their families **T**o **L**ive well **F**ollowing cancer-**A**dolescent and **Y**oung **A**dult version), is delivered to groups of 3–5 AYAs by a psychologist in six, weekly online sessions, shortly after cancer treatment completion. The Recapture Life-AYA program is part of the larger Recapture Life program, which includes a Recapture Life-Parents/Carers program for caregivers of recently off-treatment paediatric cancer patients.

This study employs a 3 (treatment condition) x 3 (assessment point) factorial design. All participants will be assessed using a battery of measures at baseline (T1: recruitment), post-treatment (T2: seven weeks after T1) and 12 months following participation in Recapture Life-AYA or the PSG control (T3). These measures will include a measure of QoL, as well as measures assessing AYAs’ anxiety, depression, and family functioning.

### Study aims and hypotheses

This phase II randomised controlled trial (RCT) aims to assess:

1. The efficacy of Recapture Life-AYA in improving QoL in AYA cancer survivors. In addition to assessing QoL (the primary study outcome), secondary outcomes assessed will include depression, anxiety and family functioning.

2. The feasibility of implementing Recapture Life-AYA Australia-wide, including the recruitment procedure, response/attrition rates and cost.

We hypothesise that shortly after intervention, and at the 12 month follow up:

1. Both the PSG control and Recapture Life-AYA groups will show improved QoL and other secondary psychological outcomes compared with the waitlist control.

2. Recapture Life-AYA will improve participants’ QoL, depression, anxiety, and family functioning to a greater extent than will the PSG control group.

3. Participation in Recapture Life-AYA will prove feasible and economical.

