### Procedures

Following recruitment, participants will complete an intake interview with the study psychologist ([name]) to further screen for participant eligibility, orient participants to the study procedures, and ascertain the suitability of the participant’s internet connection. The intake interview will also serve to build rapport with the psychologist, by providing AYAs the opportunity to discuss their cancer experiences, current needs, and personal goals in participating in the study.

Participants will then be randomly allocated to one of the three study arms. The research assistant will send a hired (insured) laptop to any participants who do not have computer access two weeks before the commencement of each online group. This process will ensure equity (all participants will have access to identical equipment), minimise technical challenges (required software/hardware will be pre-installed) and will maximise security (security settings will be pre-set by the technical support person). All equipment will be returned after study participation. Participants randomised to the Recapture Life-AYA condition will also receive a written manual summarising the weekly home practice activities.

During Weeks 1–6 of each 12 week block, those allocated to Recapture Life-AYA and the PSG will participate in their allocated intervention. In Week 7, all participants will complete their second assessment (T2). For waitlist controls, this assessment will also serve as their T1 (pre-intervention) assessment. In Week 7, waitlist participants will be randomly allocated to either Recapture Life-AYA or PSG (completed during weeks 7–12). Waitlist participants will then complete a second T2 assessment, one week after their intervention.

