#### Statistical analyses

This trial will employ ‘Intention to treat’ and ‘as treated’ analyses. Analyses will be based on mixed random-intercept models which will assess differences between the groups in terms of change in QoL from T1 to T2, and from T1 to T3. Random intercept models, which utilise maximum-likelihood estimation, provide more efficient estimates of effects with unbalanced data than the traditional repeated measures approach 
[81]. Analyses will follow recent commentaries on the best way to manage missing data by employing multiple imputation techniques 
[82]. Multiple regression analyses will also be conducted using T1 data to identify demographic and other factors that contribute to treatment outcome. Multiple comparisons will be used to test a priori and post-hoc hypotheses, appropriately adjusted to maintain the nominated Type I error rate.

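### Hypothesis 1 claims a 12-month benefit over waitlist, but waitlist participants are allocated to an active programme in Week 7, so that half of it cannot be tested

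*Protocol article*

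**What the plan says.** Study aims and hypotheses opens its list with "We hypothesise that shortly after intervention, and at the 12 month follow up". The first item beneath reads: "Both the PSG control and Recapture Life-AYA groups will show improved QoL and other secondary psychological outcomes compared with the waitlist control". That opening governs the item, so the comparison with waitlist is claimed at both time points, for quality of life (QoL) and for the secondary outcomes.

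Methods/Design lists the arms as "Recapture Life-AYA, a peer-support group (PSG) control, and a six week waitlist control group". It describes a design of three conditions by three assessments, and dates T3 at 12 months after taking part in RL or the PSG.

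Procedures states: "In Week 7, waitlist participants will be randomly allocated to either Recapture Life-AYA or PSG (completed during weeks 7–12". No exception is given. Of the Week 7 assessment it says: "For waitlist controls, this assessment will also serve as their T1 (pre-intervention) assessment". It then adds: "Waitlist participants will then complete a second T2 assessment, one week after their intervention".

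Statistical analyses names both intention-to-treat and as-treated analyses, using models that "assess differences between the groups in terms of change in QoL from T1 to T2, and from T1 to T3". It does not limit the T1-T3 comparison to particular arms.

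**The concern.** A comparison with waitlist at 12 months needs a group that is still waiting at 12 months, or at least one whose outcome can stand in for no intervention. The procedures end the waiting period at Week 7 for the whole arm. The hypothesis, the three-by-three design and the T1-T3 group comparison all presuppose a waitlist condition at T3 that the procedures do not provide.

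What is at stake is half of the first efficacy hypothesis. If the T3 comparison is run on the arms as randomised and reported under hypothesis 1, its result will not bear on whether either programme is better than waiting. That holds whether the result is positive, null or negative.

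**Working it through.** **1. The plan's own figure.** Participants gives d = 0.65 for the T1-T2 change between any pair of groups, 80% power, two-sided 0.05 and 90 participants. The allocation ratio is not stated, so 30 per arm is an assumption.

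Power = Φ(d√(n/2) − 1.96) = Φ(0.65 × √15 − 1.96) = Φ(2.517 − 1.960) = Φ(0.557) = 71.1%. The t-test version gives 69.7%.

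The stated 80% is not reproduced on this reading. It would need 38 to 39 per arm, or a one-sided 0.05 test (80.9%), or d scaled on the raw-score SD with a T1-T2 correlation of about 0.60, which the article does not give. That is a separate matter and nothing below depends on it. What matters here is that the sizing refers to T1-T2 change only.

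**2. Tracing each arm.**

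| Randomised to | Weeks 1-6 | State at T2 (Week 7) | Weeks 7-12 | State at T3 |
|---|---|---|---|---|
| RL | RL | RL received | none | RL received |
| PSG | PSG | PSG received | none | PSG received |
| Waitlist | none | untreated | RL or PSG | RL or PSG received, about six weeks later |

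With 30 per arm, untreated waitlist participants by design number 30 of 30 up to Week 7 and 0 of 30 at T3. Because T3 is counted from each person's own programme, it also falls about six weeks later after randomisation for the waitlist arm.

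**3. The two named analyses at T3.**
- As treated: with an even second allocation and no attrition there are 30 + 15 = 45 RL, 45 PSG and 0 waitlist. The contrast in hypothesis 1 does not exist.
- Intention to treat: the original waitlist arm can be compared, but the contrast is immediate versus delayed active intervention.

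**4. What the as-randomised T3 contrast estimates.** Let R and P be the 12-month gains of RL and PSG over no intervention, p the share of the waitlist arm sent to RL, and c the benefit lost through delay. None of these is given in the article.

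Mean gain of the original waitlist arm = pR + (1 − p)P − c.

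- RL minus waitlist = (1 − p)(R − P) + c
- PSG minus waitlist = −p(R − P) + c

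The contrasts depend only on the RL-PSG difference, the split and the delay. The size of the benefit over no intervention drops out.

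Illustrative values, all with 30 per arm and c = 0:

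| R − P (SD) | p | RL minus waitlist | PSG minus waitlist | Power per contrast |
|---|---|---|---|---|
| 0.65 | 0.5 | 0.5 × 0.65 = +0.325 | −0.325 | Φ(0.325√15 − 1.96) = Φ(−0.701) = 24% |
| 0.325 | 0.5 | +0.1625 | −0.1625 | Φ(0.1625√15 − 1.96) = Φ(−1.331) = 9% |
| 0 | any | 0 | 0 | type I error only |

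Varying the split at R − P = 0.65: p = 0.4 gives +0.39 and −0.26; p = 0.6 gives +0.26 and −0.39. A cost of delay moves both contrasts upward. At p = 0.5 and R − P = 0.65, PSG minus waitlist is negative only while c is below 0.325 SD.

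**The case against.** The best reply is that the intended scope can be read from elsewhere in the article. The waitlist is described as lasting six weeks. The Discussion justifies it by short-term concerns (distress easing soon after treatment ends, services changing during recruitment) and frames the long-term question as RL against peer support. The sample size rests on T1-T2 change. On this view the fault is one opening phrase shared by two hypotheses, plus an unspecific T1-T3 sentence. This stands as an account of how the problem arose, and it shows that the correction fits the authors' own rationale. It does not remove the contradiction: the opening phrase covers hypothesis 1, and no analysis plan could supply an untreated group at 12 months.

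A reader might also infer more than the article supports:
- *That the waitlist arm vanishes at T3.* It can still be followed as randomised. Immediate versus delayed intervention is a valid contrast, but not the one in hypothesis 1.
- *That PSG must look worse than waitlist at T3 if hypothesis 2 is true.* This needs a cost of delay smaller than p(R − P). The article says the recruitment window was chosen to deliver the skills early in survivorship, so a cost of delay cannot be ruled out.
- *That d = 0.65 is the plan's 12-month effect.* It is defined for T1-T2 change, and no second-allocation ratio is stated.
- *That waitlist participants enter one model as both controls and treated.* Procedures relabels their assessments, but Statistical analyses does not say that the relabelled records are pooled with the first phase. That handling may sit in the analysis plan, and the study flowchart is not reproduced in the text.
- *That a null T3 result will be reported as lost benefit.* No passage plans that interpretation.

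**Conclusion.** The contradiction holds on the text alone and needs no outside figure. Hypothesis 1 is stated at 12 months against a waitlist that ends at Week 7, so its 12-month half cannot be tested under either named analysis. A T3 contrast with the original waitlist arm is evidence neither for nor against a benefit over waitlist.

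The figures of ±0.325 SD and about 24% power are illustrations. They rest on a 50:50 second allocation, no effect of delay, 30 per arm and an RL-PSG difference of 0.65 SD persisting to T3. The more general result, given no effect of delay, is that both contrasts are zero whenever RL and PSG are equally effective, whatever their benefit.

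The comparison with waitlist on T1-T2 change and the RL versus PSG comparison at T3 both remain available. The text needs correcting because a stated efficacy hypothesis cannot be answered by the design, not because the trial as a whole fails.

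**What to change.** In Study aims and hypotheses, limit hypothesis 1 to the post-intervention assessment (T2), and keep the 12-month hypothesis for RL versus PSG only.

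In Statistical analyses, state three things:
1. T1-T3 change is tested for RL versus PSG.
2. Any T3 contrast with the original waitlist arm is immediate versus delayed intervention, and is labelled so.
3. Data from waitlist participants after Week 7 are not counted as waitlist control data.

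Make no 12-month claim against waitlist. Whether re-allocated waitlist participants also contribute to the RL versus PSG comparison is an optional choice for the analysis plan, and this correction does not depend on it.

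The cost is wording only. The trial gives up a 12-month claim that its design could not have supported.

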### Participants

This study will recruit 90 AYA participants from hospitals across Australia in the first 1–6 months after treatment completion. AYAs will also have the option of inviting a support person to receive information and updates through the Recapture Life-AYA study, however as this is optional no ‘target’ sample size of support persons has been set. The AYA sample size will allow differences of a medium to large effect size (*d* = 0.65, the difference in change from T1 to T2 for any pair of groups, standardised on the pooled within-group standard deviation) on the primary outcome variable (QoL) to be detected with a power of 80% at a significance level of 0.05 (two-tailed). This effect size is clinically significant 
[42] and is based on other RCTs of similar interventions for AYAs with chronic illness 
[43-45]. It is anticipated that approximately 220 patients will need to be approached to achieve a final sample of 90 participants (assuming a response rate of 50% and attrition rate of 20%, based on previous interventions with AYA) 
[19,46,47].

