In addition, the strict treatment fidelity assessments involved in this trial will enable an examination the relative benefits of a structured, CBT-based intervention when compared with a non-directive, peer support group model. It is possible and likely that although the psychologist facilitator does not teach the same structured, CBT-based coping skills in the PSG, peer-discussion may nevertheless facilitate spontaneous discussion around adaptive coping skills, maladaptive/unhelpful thinking styles, or stress reduction strategies for example. The treatment fidelity assessments, including the coding of a random sample of 15% of sessions for cognitive content, will ensure an examination of the extent to which such skills-based discussion is facilitated, or directed, by the Recapture Life-AYA facilitator, and the proportion of session time spent on discussing adaptive coping strategies. Consequently, although there may be a reasonable degree of content overlap between the PSG and the Recapture Life-AYA groups, the rigorous treatment fidelity processes in this trial will mean that it is still possible to distinguish between the two arms in terms of mechanisms of change. This is critical in order to make recommendations for future intervention design.

The innovative videoconferencing delivery method used in Recapture life involves inherent challenges. There is growing evidence supporting the promise of this method in treating a number of disorders (e.g., Obsessive-Compulsive Disorder) 
[87]. Evidence suggests that several core aspects of CBT such as cognitive challenging, role-playing and modeling, setting up behavioural experiments and homework assignments, will translate well over videoconferencing methods 
[88]. Further, videoconferencing methods do not appear to diminish therapist competence, adherence, or patient perceptions of rapport or empathy conveyed by the therapist 
[89]. However, as most ‘online therapies’ are self-guided by the user with either telephone/email-based clinician support 
[90], few manualised treatment programs or best-practice guidelines exist to support the therapist in aspects relating to therapy process and online interaction. This may mean that therapist practice effects occur across the study period, as the therapist gains competency in anticipating, and managing, challenges in the videoconferencing environment.

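### One planning effect (d = 0.65 with 80% power) is claimed for every pair of arms, although the hypotheses order the arms, so unless Recapture Life beats waitlist by at least 1.30 SD one hypothesised contrast falls below the stated power

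*Protocol article*

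**What the plan says.** The protocol article's Participants section states "This study will recruit 90 AYA participants from hospitals across Australia" and says this number gives 80% power, at a two-tailed 0.05 level, for d = 0.65 on the primary quality-of-life outcome. The d is "the difference in change from T1 to T2 for any pair of groups, standardised on the pooled within-group standard deviation". Two reasons are given for its size: it is described as clinically significant, and it "is based on other RCTs of similar interventions for AYAs with chronic illness". The comparators in those trials are not named.

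Study aims and hypotheses makes directional statements about all three pairs. Hypothesis 1: "Both the PSG control and Recapture Life-AYA groups will show improved QoL and other secondary psychological outcomes compared with the waitlist control". Hypothesis 2: RL will improve outcomes "to a greater extent than will the PSG control group".

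The Background says of peer-support groups that "the few that have been formally evaluated tend to show small/mixed effects among AYAs". The Discussion accepts that "there may be a reasonable degree of content overlap between the PSG and the Recapture Life-AYA groups".

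Under Procedures, at Week 7, "waitlist participants will be randomly allocated to either Recapture Life-AYA or PSG (completed during weeks 7–12"). Their Week-7 assessment serves as a new pre-intervention baseline, and they have their own post-intervention assessment one week after finishing.

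**The concern.** A single planning effect with a single power figure tells the reader that each of the three comparisons is equally well provided for. The hypotheses make that hard to achieve. If PSG lies between waitlist and RL, the RL-versus-waitlist difference is the sum of the other two, and the three differences cannot all equal 0.65.

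The comparison most exposed depends on which pair the 0.65 describes, and the article does not say. If it describes RL versus waitlist, RL versus PSG is underpowered. If it describes RL versus PSG, then with a small peer-support effect PSG versus waitlist is the weak one. The Discussion presents RL versus PSG as the test of whether structured skills training adds anything to peer support, with clinical and economic consequences. Readers therefore need to know how much power that contrast has.

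The design also re-randomises the waitlist third to RL or PSG, but the sizing statement is framed on the three initial arms and takes no account of this extra randomised information.

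**Working it through.** **Inputs.** From Participants: N = 90, d = 0.65, two-sided alpha 0.05, power 80%, response 50%, attrition 20%, about 220 approached. Since 220 × 0.5 × 0.8 = 88, the 90 is already net of attrition. The allocation ratio is not stated; I assume 1:1:1, so 30 analysed per arm. The peer-support effect is not quantified; I take 0.20 to 0.30 as an assumed reading of small.

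**Formula.** Two-sample t test on T1–T2 change with n per arm: noncentrality = d × √(n/2), degrees of freedom 2n − 2, no multiplicity adjustment.

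**The plan's own figure.** With n = 30 and d = 0.65, noncentrality = 0.65 × √15 = 2.517 and the critical t on 58 df is 2.002, giving power 69.7%. The stated 80% is not reproduced on this reading. It would need 39 per arm (80.9%). If d were standardised on raw scores with an assumed T1–T2 correlation of about 0.60, 30 per arm would give about 80% (normal approximation). The basis of the 80% therefore needs stating in any case, but the point below does not depend on it.

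**Additivity.** On a common within-group SD:

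(RL − waitlist) = (RL − PSG) + (PSG − waitlist).

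- If both terms on the right are at least 0.65, RL − waitlist is at least 1.30.
- If RL − waitlist is 0.65, the smaller term on the right is at most 0.65 / 2 = 0.325.

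**Power by scenario, 30 per arm (d, then power).**

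| Scenario | RL v waitlist | PSG v waitlist | RL v PSG |
|---|---|---|---|
| 0.65 is RL v waitlist; PSG effect 0.20 | 0.65, 70% | 0.20, 12% | 0.45, 40% |
| 0.65 is RL v waitlist; PSG effect 0.30 | 0.65, 70% | 0.30, 21% | 0.35, 27% |
| 0.65 is RL v waitlist; equal split | 0.65, 70% | 0.325, 24% | 0.325, 24% |
| 0.65 is RL v PSG; PSG effect 0.20 | 0.85, 90% | 0.20, 12% | 0.65, 70% |
| All pairs at least 0.65 | 1.30, over 99% | 0.65, 70% | 0.65, 70% |

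Only the last row puts every contrast at or above 0.65. It requires a peer-support effect of 0.65, which sits badly with the Background's description. Raising n to 39 per arm does not remove the problem: power at 0.325 is then 29%.

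**Using the re-randomised waitlist for RL v PSG.** If the 30 waitlist participants split equally, each active arm has 30 + 15 = 45. At d = 0.65, noncentrality = 0.65 × √22.5 = 3.083.

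| d (RL v PSG) | 30 per arm | 45 per arm |
|---|---|---|
| 0.65 | 70% | 86% |
| 0.45 | 40% | 56% |
| 0.325 | 24% | 33% |

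**The case against.** The strongest reply is that Participants words 0.65 as a difference the sample can detect, not as a forecast that all three pairs differ by that much. With equal arms and a common SD, the detectable difference is the same for every pair whatever the order of the means, and sizing to a clinically important difference is legitimate. This stands: the sizing statement and the hypotheses do not contradict each other in a strict sense.

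A reader might go further and infer that 0.65 cannot be a realistic target against both comparators, or that it was really the RL-versus-waitlist effect. The documents support neither. RL better than PSG by 0.65 and better than waitlist by 0.85 fits both hypotheses with a small peer-support effect. The comparators of the cited trials are not given. The Background also reports medium to large effects for skills-based programmes, which counts against an equal split of the benefit.

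A reader might also infer that a non-significant RL versus PSG result is to be taken as equivalence. The article says nothing of the kind.

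Last, the article does not exclude the re-randomised waitlist from the RL versus PSG analysis, and a full analysis plan could include it. That is fair, so the pooled analysis is offered as an available gain, not as the repair of an error. None of this rescues the flat power statement. The 0.65 is also justified from other trials, so it is offered as plausible, and for PSG versus waitlist the article's own evidence points lower.

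**Conclusion.** The concern holds in a limited form. One effect and one power figure for every pair do not describe the power of the three hypothesised contrasts. Unless RL exceeds waitlist by at least 1.30, at least one contrast falls below 0.65 and below the stated power. Which one it is cannot be settled from the article. Over effects of 0.20 to 0.45, power at 30 per arm is about 12% to 40%, and at 0.65 itself it is about 70%.

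These figures assume 1:1:1 allocation, 90 analysed participants, d standardised on the SD of change, and no multiplicity adjustment. The adjustment promised under Statistical analyses would lower them. The 45-per-arm figures further assume an equal split of the waitlist, complete follow-up and the same RL versus PSG effect in both phases.

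**What to change.** 1. In Participants, describe 0.65 as a minimum difference of interest and state which comparison the cited trials support. Replace the flat 80% with the actual power for RL versus waitlist, PSG versus waitlist and RL versus PSG over a stated range of effects, giving the allocation ratio and the SD basis.

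2. For the post-intervention RL versus PSG contrast, analyse everyone randomised to RL or PSG. This includes the waitlist participants re-randomised at Week 7, with their Week-7 score as baseline and their own post-intervention assessment as outcome, plus a term for phase (immediate or delayed). Keep both waitlist contrasts on first-phase data only.

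Reporting RL versus PSG with a 95% confidence interval is sensible practice, though no statement in the article needs correcting on that account.

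The cost is a rewritten sample-size paragraph, a sentence or two in the analysis section and one model term. No new patients, visits or data are needed. The downsides are small: the stated power looks less favourable, and delayed participants start about six weeks later after cancer treatment, which the phase term is there to absorb. Pooling does not bring power to 80% at 0.45, so the first change is needed even if the second is adopted.
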